### Impact of fibromyalgia

We will assess the impact of fibromyalgia using the FIQ-R, an instrument validated for the Brazilian population by Lupi et al. (2016) [42], with adequate reliability and internal consistency [43]. The FIQ-R is used for assessments at week 1, 6, 12, and 24. It consists of 21 items assessing function (items 1–9), global impact (items 10–11), and symptoms (items 12–21). All questions relate to experiences during the past 7 days and are presented on an 11-point numerical rating scale (from 0 to 10). A normalization factor is applied to each of the three domain scores: the functional domain score is divided by 3, the global impact domain score is divided by 1, and the symptom domain score is divided by 2. The total FIQ-R score (from 0 to 100) is obtained by summing the three normalized domain scores. Thus, the lower the score, the lower the impact of fibromyalgia on the individual’s overall quality of life. A reduction of 27 points is considered to be the minimum clinically important difference [36], although this may change in new studies [43].

### Pain

We will assess pain with different instruments and tests. We will assess pain intensity with the Numeric Pain Rating Scale (NPRS), a self-report instrument validated in Portuguese by Ferreira-Valente et al. (2011) [44] NPRS has a sequence of numbers (from 0 to 10), where 0 represents “no pain” and 10 represents “the worst pain imaginable”. This instrument is used in tests of temporal summation (wind-up mechanism) and conditioned pain modulation (diffuse nociceptive inhibitory control). A 2-point reduction [45] in pain intensity is considered a clinically important minimal difference [46].

We will assess the cutaneous sensory threshold by means of an esthesiometry test using a set of von Frey filaments (North Coast®, Gilroy, CA, USA) in the trapezius, supraspinatus and sternocleidomastoid muscles [47]. The filaments have increasing values of compressive force (in mN), which will be tested by calibration on a precision analytical balance (CQA®, Paulínia, SP, Brazil). All subjects are blindfolded and each filament, in order of increasing force, is positioned perpendicular to the subject’s skin, gently pressed until its initial curvature, and then removed. The first filament that the individual reports having perceived touch will be considered as the cutaneous sensory threshold, so we will record the pressure force value corresponding to the reported threshold [48].

We evaluate the wind-up mechanism by means of the temporal summation test using a digital pressure algometer (ITO® brand, Tokyo, Japan), whose reliability has already been tested (Intraclass Correlation Coefficient [ICC] = 0.815) [49]. The test verifies the wind-up mechanism, which is characterized by the progressive and frequency-dependent facilitation of a neuron’s responses observed during the application of repetitive or continuous stimuli of constant intensity [50]. A pressure of 2.5 kg is applied to the anterior surface of the subject’s right forearm (7.5 cm from the distal crease of the wrist). This pressure is maintained for 30 s; during the continuous stimulus, the individual is asked about the intensity of pain felt at the 1st, 10th, 20th, and 30th second of stimulus application (using the NPRS) [51],44].

We will assess diffuse noxious inhibitory control using the conditioned pain modulation test [52], which is a phenomenon in which, under normal conditions, the perception of pain to a tested stimulus is reduced by the application of another painful stimulus (conditioned stimulus) [53]. The test will be divided into three stages: First, we will measure the pressure pain threshold on the anterior surface of the subject’s right forearm, 7.5 cm from the distal wrist crease, using a pressure algometer (ICC = 0.815) [49] to stimulate a level 4 pain (via NPRS). Second, ischemic compression (conditioned stimulus) is applied to the subject’s left arm using an analog sphygmomanometer placed 3 cm proximal to the cubital fossa. When 250 mmHg of pressure is reached, the individual is asked about the intensity using the NPRS. If the individual reports pain < 5, we will ask for flexion and extension of the elbow so that the pain increases to a level ≥ 5, and then we will reassess the pressure pain threshold on the anterior surface of the individual’s right forearm (using the pressure algometer to stimulate a level 4 pain simultaneously with the conditioned stimulus). Finally, after measuring the pressure pain threshold during the ischemic stimulus, we will remove the compression and after 30 s and then after 5 min, we will measure and record the pressure pain threshold again (using a pressure algometer to stimulate a level 4 pain on the anterior surface of the individual’s right forearm) [54].

### Sleep quality

We will assess sleep quality using the Pittsburgh Sleep Quality Index (PSQI) for sleep quality, adapted for Brazilians by Bertolazi et al. (2011) [55] It is a reliable instrument (ICC = 0.65) [56] that assesses seven sleep components: subjective quality, sleep latency, sleep duration, sleep efficiency, sleep disturbances, medication use, and daily dysfunction. For each component, the score varies from 0 to 3, and the sum gives a maximum score of 21. Scores above 5 indicate poor sleep quality.

### Anxiety and depression

We will assess anxiety and depression using the Hospital Anxiety and Depression Scale (HADS), validated for Brazilians [57]. It consists of 14 items divided into two domains (depression and anxiety) with seven items each. The items have a 4-point Likert scale (from 0 to 3), resulting in total scores ranging from 0 to 21, both for anxiety and depression. The cut off points indicating moderate to severe symptoms are: anxiety domain ≥ 8 and depression domain ≥ 9.

### Ability to walk

We will assess walking ability using the 6-minute walk test (6MWT) (CCI > 0.90) [58]. We will instruct the individual to walk at the highest possible speed during the 6 min and to stop the test if they feel uncomfortable. Before and after the session, the following variables will be monitored: systemic blood pressure, heart rate, peripheral oxygen saturation, and respiratory rate. During the session, fatigue levels (leg and respiratory) are monitored using the Borg scale. An increase of 156 to 167 m in distance walked is considered a clinically important minimum difference in individuals with fibromyalgia [59]. This test will be done before and after treatment (week 1 and week 12).

### Isokinetic dynamometry

The individuals will be positioned with the hip angle at 100º (trunk, pelvis, and thigh will be stabilized with straps). The axis of rotation of the dynamometer will be aligned with the axis of the knee, at the level of the lateral epicondyle of the femur, fixed to the distal part of the leg, approximately 5 cm above the medial malleolus. Correction for the effect of gravity will be calculated with the limb at 60° of flexion (according to the equipment instructions). We will evaluate these variables using the isokinetic dynamometer (Biodex Medical Systems 3®, Shirley, New York, USA).

A familiarization series of three submaximal isokinetic contractions is performed prior to the isokinetic assessment. 3 min after the familiarization, the subjects will perform five concentric isokinetic contractions of knee extension, from 90° to 15° (considering 0° as full extension), with a total range of motion of 75°, at an angular velocity of 60º/s (series of five repetitions), for the analysis of the variables torque peak normalized by body mass, power and work [60]. Verbal encouragement, as well as visual feedback from the equipment, will be given in an attempt to reach the maximum level of voluntary effort during all the contractions that each subject will perform. The same procedure will be repeated with the contralateral limb 5 min after the end of the dominant limb [61]. This test will be performed before and after treatment (week 1 and week 12).

### Maximal dynamic strength for exercise load

We will determine the maximum dynamic strength for exercise load using the 1 repetition maximum (1-RM) test [10]. The results of this test, in addition to being reliable (CCI > 0.90) [62], are widely used to control the intensity of resistance exercises based on the percentage of maximal dynamic strength in individuals with fibromyalgia. The individual will perform 10 repetitions of the movement (without load) for the purpose of musculoskeletal warm-up and understanding of technique. After 1 min of rest, they will perform 3 to 5 self-reported maximum repetitions, then after 3 min of rest, they will perform the 1-RM test [63].

In addition, as an alternative to confirm the test result, we will estimate the maximum dynamic strength using the mathematical equation proposed by Brzycki [64]: 1-RM = submaximal load in kg / (1.0278–0.0278 × number of repetitions). The test is used for evaluations at week 1, week 4, and week 8 to adjust the intensity of resistance training.

### Global perceived effect regarding treatment

We will assess the self-reported global perceived effect of treatment using the Global Perceived Effect (GPE) scale, an instrument validated for the Brazilian population by Costa et al. [65]. It is an 11-point descriptive scale in which the progression (or regression) of the individual’s clinical condition is classified according to their score at a given time. Thus, the individual will report their perception of improvement in the face of the intervention through a score classified as: -5 (much worse), 0 (no change), and + 5 (fully recovered). We will use the GPE at three assessments (6th, 12th, and 24th week). A change of 3 points is considered a clinically important minimum difference.

### Intervention overview

All groups will receive a 45-minute pain education session prior to the exercise program that addresses the pathophysiological mechanisms of chronic pain, strategies for coping with pain, avoiding hypervigilance, and deconstructing beliefs and myths about chronic pain (e.g., the degree of diagnostic uncertainty of the imaging exams) [66].

Before the first resistance training session, there will be a period of familiarization, followed by the 1-RM test in each of the exercises proposed in the resistance training program (Fig. 3). All sessions will take place individually, in a private room with lighting and air conditioning at 23 °C. All exercises will be performed by a Bachelor of Physical Education with experience in exercising individuals with chronic pain. Individuals will receive 24 exercise sessions. Two sessions per week, for 40 min and 10 min of rest after the exercise session, according to the guidelines of the American College of Sports Medicine [67], as well as clinical trials that tested this guideline in individuals with fibromyalgia [16, 17].

Each individual is instructed to discontinue the intervention at any time if they do not wish to continue with the proposed exercise session. In addition, before and after the exercise session, blood pressure (using a sphygmomanometer and stethoscope), heart rate and peripheral oxygen saturation (using an oximeter), generalized pain intensity (using the NPRS), and subjective perception (using the Borg scale) will be monitored [68].

### Group 1 (Progressive intensity, experimental)

Firstly, individuals will perform a global warm-up of four exercises (Fig. 3) without load: seated calf raise (1 min), lateral dumbbell raise (1 min), leg press (1 min), and incline bench press (1 min) [69, 70]. They will then perform moderate intensity resistance training (50% of maximum dynamic strength). Individuals work nine muscle groups (gluteus, quadriceps, hamstrings, biceps brachii, triceps brachii, pectoralis major, calf, deltoid, and latissimus dorsi) through six different exercises in the following order: seated calf raise, knee extension machine, seated row machine, dumbbell lateral raise, leg press, and incline bench press [21].

Based on 50% of the maximum dynamic strength as the initial parameter for moderate intensity in resistance training [17, 21], the load in kg will be previously identified through the 1-RM test in the proposed exercises. The individual’s muscular strength will be individually reassessed every 4 weeks (via 1-RM) and the intensity of each exercise will receive a positive adjustment of 20% of the value observed in kg (i.e., first month 50%; second month 70%; third month 90% of the maximal dynamic strength – Table 2) [17, 21].

**Table 2 Tab2:** Description of the intensity of physical exercise programs

Group (intensity)	1st Month	2nd Month	3rd Month	Follow-up
1. Progressive intensity (experimental)	50% (1-RM test)	70% (1-RM test)	90% (1-RM test)	Nonexercise
2. Constant intensity (control A)	50% (1-RM test)	50% (1-RM test)	50% (1-RM test)	Nonexercise
3. Walking (control B)	60-70% (HRmax)	60-70% (HRmax)	60-70% (HRmax)	Nonexercise

1-RM test: 1-repetition maximum test; HRmax: maximum heart rate. The external load (intensity) will be adjusted on the basis of the new values observed in the 1-RM (every 4 weeks)

The intensity of the exercises (total load in kg), the interval between sets (rest in seconds), the volume (number of sets, repetitions and time under tension) as well as the frequency of the resistance training will be controlled by the researcher with experience in chronic pain. Twice a week (for 3 months), individuals with fibromyalgia will perform three sets of each exercise: 10 repetitions, 40 s of muscle tension, full range of motion, inspiration during the eccentric phase of the movement, and 60 s of rest among sets [71]. In order to maintain the same volume of exercises in resistance training (according to the intensity progression), we will add 20 s of rest to the rest among sets (i.e., first month 60; second month 80; third month 100 s of interval), because higher intensities, while maintaining the same volume of work (sets, repetitions, and time under tension), require longer intervals of rest [72].

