Evidence-based practice suggests that we should follow a tripod for health interventions: scientific evidence, professional knowledge, and patient preference [18, 19]. In this context, Andersson et al. [20] found that women with fibromyalgia prefer resistance exercises with adjusted intensity using free weights (i.e., resistance training), because the higher the load in kg (intensity) used to resist the movement, the shorter the time under muscle tension, and consequently the lower the level of stress and muscle fatigue (during and after exercise). High-intensity resistance training is also safe for people with fibromyalgia [17, 21].

However, only two systematic reviews have examined this scenario [18, 21]. The first study [17] suggests that resistance training at moderate or high intensity improves physical function in women with fibromyalgia. The second study [21] suggests the frequency (twice a week), intensity (40–80% of maximum dynamic strength), volume (1 to 2 sets of 4 to 12 repetitions of the movement), and target muscle group (gastrocnemius, quadriceps, hamstrings, pectorals, latissimus dorsi, rhomboids, deltoid, biceps, and triceps).

It is important to note that although exercise has not been shown to increase pain during its performance [22], muscle contraction can cause pain [23], and greater exercise intensity can elicit greater pain sensations, which may interfere with treatment adherence [24]. An alternative to reduce this side effect is to progressively increase exercise intensity, with loads gradually added according to biological adaptations [25]. Some studies have used this strategy in patients with fibromyalgia [22, 26–28], but the results are controversial [27–32] and the comparison between groups did not control for the progression of exercise intensity [27–32]. Studies that have used progressive intensity resistance training in patients with fibromyalgia have found reductions in disability [29] and fatigue [30].

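### Month 3 asks Group 1 for 10 repetitions per set at 90% of 1-RM, while the protocol's own equation predicts about 4.6 on average and 10 only at about 75%

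*Protocol article*

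**What the plan says.** The section on Group 1 and Table 2 set the experimental load at 50%, 70% and 90% of 1-RM in months 1, 2 and 3: "third month 90% of the maximal dynamic strength". The reference strength is the most recent test, as the Table 2 footnote states: "The external load (intensity) will be adjusted on the basis of the new values observed in the 1-RM (every 4 weeks". The section on maximal dynamic strength gives the schedule: "The test is used for evaluations at week 1, week 4, and week 8 to adjust the intensity of resistance training". The week-8 value therefore governs month 3.

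The volume is the same for all three months: "individuals with fibromyalgia will perform three sets of each exercise: 10 repetitions, 40 s of muscle tension, full range of motion". Only rest between sets changes (60, 80, then 100 s), because higher intensities, "while maintaining the same volume of work (sets, repetitions, and time under tension), require longer intervals of rest".

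The section on maximal dynamic strength also gives a prediction equation to confirm the test result: "1-RM = submaximal load in kg / (1.0278–0.0278 × number of repetitions" (the bracket closes there). In the Introduction, the second of the two systematic reviews (reference 21) is reported as suggesting "intensity (40–80% of maximum dynamic strength), volume (1 to 2 sets of 4 to 12 repetitions of the movement" (the bracket closes there too).

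**The concern.** A load close to the single-repetition maximum can be lifted only a few times, yet the plan asks for 10 repetitions in each of three sets over six exercises at 90%. If the protocol's own equation says that this is out of reach on average, either the repetitions or the stated percentage must give way.

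Progression of intensity is the experimental variable. Month 3 is 8 of the 24 sessions, has the widest contrast with Group 2 (90% against 50%), and comes just before the week-12 assessment. If repetitions fall short, the two resistance arms differ in volume as well as intensity. If all 10 are completed, the load was not 90% of true strength. In both cases, clinicians would be told that a dose was tested that was not the one delivered.

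**Working it through.** **Inputs.** Loads of 50%, 70% and 90% (Group 1 section, Table 2). Three sets of 10 repetitions with 40 s of tension, read as 40 s per set (Group 1 section). Equation: 1-RM = load / (1.0278 − 0.0278 × r), where r is the number of repetitions (section on maximal dynamic strength).

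**The plan's progression.** 50 + 20 + 20 percentage points gives 50/70/90%, which matches the text and Table 2.

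**Equation solved for repetitions.** With p = load/1-RM, r = (1.0278 − p)/0.0278.

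| Month | p | Predicted repetitions to failure | Prescribed |
|---|---|---|---|
| 1 | 0.50 | 0.5278/0.0278 = 19.0 | 10 |
| 2 | 0.70 | 0.3278/0.0278 = 11.8 | 10 |
| 3 | 0.90 | 0.1278/0.0278 = 4.6 | 10 |

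The load at which 10 repetitions is the maximum is 1.0278 − 0.278 = 0.7498, about 75%. The conflict is confined to month 3. Longer rest between sets does not resolve it, because the limit already applies to the first set.

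**A check within the protocol.** The 1-RM procedure includes a step of 3 to 5 maximal repetitions. By the equation these correspond to 1.0278 − 0.0834 = 94% and 1.0278 − 0.139 = 89% of 1-RM. The month-3 load lies in that range.

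**What would make 10 repetitions possible (assumed values).**

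- Strength gain g after week 8, p = 0.90/(1 + g): 6.1 repetitions at 5%, 7.5 at 10%, 8.8 at 15%, 10.0 at 20%. The gain needed is 0.90/0.7498 − 1 = 20%.
- 1-RM measured too low by a share u of its true value, p = 0.90 × (1 − u): 6.2 at 5%, 7.8 at 10%, 9.5 at 15%. The error needed is 1 − 0.7498/0.90 = 16.7%. Such an error is plausible here, since the Introduction notes that "muscle contraction can cause pain".
- Both together, 10% each: p = 0.90 × 0.90/1.10 = 0.736, giving (1.0278 − 0.736)/0.0278 = 10.5 repetitions for one set. The true load is then about 74% of strength, not 90%.

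**Size if the average prediction held in all three sets.** 3 × 4.6 = 13.8 repetitions per exercise per session against 30, or 46%. At 40/10 = 4 s per repetition, tension is 4.6 × 4 = 18.4 s per set against 40 s.

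**The case against.** The strongest reply is that the equation is an average prediction. The protocol uses it to confirm the 1-RM test, not to set repetitions, and gives no error band and no values for the six separate exercises. This stands. A reader might infer that most participants will fail the month-3 sets; the documents give no basis for any such proportion. It is also true that strength gain and an under-measured 1-RM can occur together, so neither has to reach its single-factor threshold. That can explain how 10 repetitions get done, but only at a true load of about 75% or less.

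A second reply concerns the sources. A reader might charge reference 21 with failing to support three sets of 10 at 90%. That goes too far. The progression is cited to references 17 and 21, and the Introduction reports the former as favouring moderate or high intensity. The set and repetition scheme is cited to reference 71 and the rest rule to reference 72. What remains is that 90% lies above the 40–80% reported from reference 21.

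Third, holding volume equal is deliberate, because it isolates intensity as the difference between Groups 1 and 2. A remedy that simply cuts repetitions would sacrifice that match. This also stands and shapes the fix.

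Finally, an article condenses the full protocol, so the absence of a per-set log is no fault; the article says that the researcher controls load, rest and volume. But the point here is not an omission: the article states both conflicting parameters and affirms that volume is maintained.

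**Conclusion.** The concern holds as an inconsistency in the stated dose. By the protocol's own equation, the month-3 load allows 4.6 repetitions on average against the 10 prescribed, and 10 correspond to about 75% of 1-RM. The statement that sets, repetitions and time under tension are unchanged at 90% is therefore unlikely to hold on average, with variation between people and exercises that cannot be quantified from the document.

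This rests on the equation being a fair average guide for these patients and exercises, and on the week-8 1-RM being the reference.

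A reader might also infer that the trial's comparison is biased or underpowered. Nothing here shows that: randomisation, the primary outcome and the intention-to-treat analysis stand, and no sample-size figure depends on this point. What is affected is what the trial may say about the dose tested in 8 of 24 sessions. It should be fixed.

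**What to change.** Amend the Group 1 section as follows:

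- Withdraw, for month 3, the statement that sets, repetitions and time under tension are maintained.
- State that at 90% of 1-RM participants do as many repetitions as they can complete with good form, up to 10.
- Record load, repetitions and tension for each set in both resistance arms, and report the intensity and volume delivered.
- Do not describe month 3 as 90% at matched volume in the conclusion unless the log shows it.

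If the sponsor prefers to fix the prescription in advance, there are two options. About 4 repetitions at 90% keeps the intensity contrast but loses the volume match: 3 × 4 = 12 repetitions per exercise per session against 30 in Group 2. At most about 75% with 10 repetitions keeps the volume match and stays within 40–80%, but narrows the contrast with Group 2's 50%. The choice is a trade-off for the sponsor.

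If month-3 sessions have already been run (the article does not give recruitment status), report what was delivered. The cost is a short amendment, a small logging burden and a less tidy dose description; no extra patients, visits or assessments are needed.
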